### Instruments

Child health care nurses, psychologists, and preschool teachers serve as informants. Behavioral problems are measured with the SDQ (25 items and a supplement with 8 items). SDQ is validated, and proposed cutoffs are available for Swedish conditions [14,26,27]. The Children’s Engagement Questionnaire (CEQ; 29 items) measures preschool children’s targeted engagement and social interaction in everyday life [28,29]. The Joint Attention Observation tool (JA-OBS; 5 items) screens for the autism spectrum [30]. Psychosocial problems in the family are measured with LAPS (*lapsen psykososiaalisen terveyden arviointimenetelmä*; English translation: child mental health assessment form) [31]. A self-constructed questionnaire collects sociodemographic and background questions, including questions on mother tongue, possible diagnosis, education, professional activities, and parental ability. The health care process, for example, the number of investigations, waiting time for assessment, visits, and satisfaction, is also compiled with a separate questionnaire. Collaboration between professionals in different organizations is assessed using the “Spider” measurement, which has 10 questions [32].

### Data Analysis

Table 1 summarizes the primary outcomes, confounders, and analysis that will be conducted. Quantitative multivariate analyses will be done in SPSS (version 28; IBM Corp), and longitudinal data will be analyzed using person- and group-centered analytic methods, cluster analysis, and path analysis. A comparison study with the control group and children referred to habilitation centers will occur. The focus group and semistructured interviews will be analyzed qualitatively with content analysis.

**Table 1 table1:** Summary of substudies included in the PLUSS.^a^

Study (design and time frame)	Study population	Informants (instruments)	Main outcomes
User study (qualitative focus group interview study, conducted 2019-2020)	Parents of a 1.5- to 5-year-old child with neurodevelopmental problems (n=13)	Parents (data collected with semistructured focus group interviews)	Satisfaction with health care system
Pilot study on children with neurodevelopmental problems (quasi-experimental quantitative study, conducted 2020-2021)	1.5- to 5-year-old children with neurodevelopmental problems (n=80)	Parents, child health care psychologists, preschool teachers (data collected with SDQ, LAPS, CEQ, JA-OBS, background questions, medical records)	Neurodevelopmental and mental health–related problems: development delay, interaction, contact difficulties, language and communication difficulties, motor difficulties, concentration/hyperactive, self-regulation, acting/boundaries, anxiety Difficulties in everyday function Psychosocial stress factors Socioeconomic status, family constellation, mother tongue, possible diagnosis, education, professional activities The health care process indicators (eg, number of assessments, visits, interventions)
Full-scale study on children with neurodevelopmental problems (quasi-experimental quantitative study with longitudinal follow-up, conducted 2022-2024)	1.5- to 5-year-old children with neurodevelopmental problems (n=160), compared to treatment as usual (n=160)	Parents, child health care psychologists, preschool teachers (data collected with SDQ, LAPS, CEQ, JA-OBS, background questions)	As above
PRIMUS parental training program (cross-sectional quantitative study, conducted 2022-2024)	Parents to a 1.5-5-year-old child with neurodevelopmental problems (n=160)	Parents (data collected with PRIMUS evaluation questionnaire, SDQ, CEQ, LAPS)	Self-rated parental ability Neurodevelopmental and mental health–related problems: development delay, interaction, contact difficulties, language and communication difficulties, motor difficulties, concentration/hyperactive, self-regulation, acting/boundaries, anxiety Difficulties in everyday function Psychosocial stress factors

^a^CEQ: Children’s Engagement Questionnaire; JA-OBS: Joint Attention Observation tool; LAPS:*lapsen psykososiaalisen terveyden arviointimenetelmä* (child mental health assessment form); PLUSS: *Psykisk hälsa Lärande Utveckling Samverkan kring Små barn* (mental health, learning, development, collaboration around preschool children); SDQ: Strengths and Difficulties Questionnaire.

### Ethics Approval

Ethics approval has been granted by the National Ethics Board (2019-04839). Informed consent is obtained from all actors: parents, managers, preschool educators, child health care psychologists, and child health care nurses. All data are registered with a participant number and encoded directly at the time of collection, considering privacy protection. The code template for translation between participant number and the test subject can be found in a logbook inaccessible to unauthorized persons. The results are reported only at the group level, where no personal data will be recognizable. All data processing follows the Swedish data law. The parents have been informed that their children will receive the standard care even if they do not participate in the study. Upon parents’ informed consent, the preschool manager and preschool teacher may consent to participate in the research, and the preschool teacher answers questionnaires.

## Results

All research included in the PLUSS model has been approved by the National Ethics Review Board (2019–04839). Informed consent will be obtained from all study participants and legal guardians if the participant is younger than 15 years. Results will be available to caregivers, professionals working with preschool children, researchers, and funders.

This study was supported by FUTURUM grants 910161 and 910441. The funders had no role in designing the study, writing the report, or deciding to submit the paper for publication.

The study has been registered at ClinicalTrials.gov (NCT04815889). The data collection for the pilot study started in April 2019, with the prior data collection period finished by April 2021. Data collection for the full-scale investigation began during May 2021 and is planned to be completed in May 2024.

## Discussion

### Principal Findings

Expected results from this study include estimates of the prevalence of neurodevelopmental problems in preschoolers, their impact on functional ability, and parental well-being. In addition, the effectiveness of the PLUSS working model is elucidated. Qualitative studies are expected to give us information about parents’ and preschool teachers’ experiences related to children with neurodevelopmental problems and how the system can support these children.

A research project conducted within ongoing clinical work provides an excellent opportunity to improve health care but is also affected by everyday obstacles. Not all activities and departments are accustomed to participating in clinical research work, and additional assignments for staff might cause skepticism to arise. The longitudinal study design will allow an analysis of changes over time in the same study participant, providing more substantial evidence for causality than could be obtained from a cross-sectional design. However, loss to follow-up may occur. Combining quantitative and qualitative approaches provides an excellent opportunity to understand the actual change in a child’s behavior with satisfaction and well-being. Another strength is that collaboration and organizational measures are studied in PLUSS.

The project is based at Jönköping County’s health care, collaborating with preschools and social services and researchers from Linköping University. Children and parents are not directly involved in the study design, recruitment, or conduct of the research. Parents are, however, engaged in focus groups that give, for example, input on how the parent educating group should be designed and what it should contain. The focus groups will involve parents of children with neurodevelopmental problems and obtain support from child health care and specialist health care. This study will be made available to the participants, the funders, professionals, researchers, and policy makers.

An important aim for future research in the PLUSS model is to follow the included children long term regarding symptom development, set diagnoses, and evaluate given interventions. Parental stress and perceived competence of parents of children with neurodevelopmental difficulties will also be considered in future research.

To improve children’s mental health in Sweden, 5 suggested, evidence-based interventions were recently published, one of them being early detection and early interventions for young people at risk for future mental health problems [33]. Current knowledge of early detection and early interventions for children suggests they have been beneficial long term and economically justifiable [5,34]. The PLUSS model has been constructed to better meet the demands of health care today with early interventions for parents and children exhibiting neurodevelopmental difficulties.

Information about the ongoing study and obtained results will be communicated via the PLUSS project’s steering group and working group within and outside the Jönköping County Region. The scientific results will be disseminated to the caregivers, professionals working with preschool children, researchers, and funders. Community policy makers and stakeholders will be targeted separately using Jönköping County’s existing information channels and conferences.

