**Methods:**

The population of interest is children aged 1.5-5 years, whom the child health care nurse refers for further assessment due to suspected neurodevelopmental problems. Data are collected using questionnaires and semistructured interviews. Measures include sociodemographic data, longitudinal data on neurodevelopmental problems, parental well-being and satisfaction, the effectiveness of parental and preschool teacher training and implementation of the model, and fostered multisectoral collaborations. Data will be analyzed with qualitative and quantitative methods.

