## Introduction

### Background

Neurodevelopmental problems among preschool children are common, with an estimated 7%-10% prevalence [1]. Early-onset externalizing or internalizing problems predict the later development of mental health problems, corresponding to or overlapping with the initial symptoms [1,2]. The earlier behavioral problems occur in a child’s life, the greater the risk [3,4].

Early identification of children with neurodevelopmental problems is crucial for providing adequate support [1,5]. Despite this knowledge, several Swedish reports have highlighted a dire need for research into the mental health of children of preschool age [6-8]. For example, data on the current prevalence of significant neurodevelopmental problems among Swedish children aged 0-5 years are missing. Inherent to this is how many of these children have been offered and are receiving any kind of intervention. In addition, studies on longitudinal trajectories of problems and provided services are scarce.

In Sweden, child health care is responsible for the early detection and follow-up of developmental problems among preschool children [9]. Swedish child health care has a well-established screening program that reaches 95% of all preschool children [10]. In addition, preschools serve as an environment where children’s problems can be identified, promoting good mental health [11]. Collaboration between child health care and preschools provides a significant opportunity to identify children and families needing support and treatment [12,13]. Standardized assessment methods, such as questionnaires, scales, and observations, with proven reliability are one way to further facilitate the early detection of emotional and behavioral problems related to neurodevelopment [14].

Despite the established health monitoring system, there is no homogeneous system of mental health services for children below school age in Sweden. Regional differences exist, and both public and private service providers are involved. Some children are referred to Child and Adolescent Psychiatry clinics, while others are assessed and followed up on by child habilitation or municipal counseling units [15]. There are also well-known shortcomings in collaborations between health actors and other multisectoral partners such as social welfare services [4]. Coordination of efforts is difficult to establish, and queues of several years for assessment and treatment are frequent.

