To study neurodevelopmental issues and the ability to function among preschool children longitudinally.To study parental well-being and satisfaction with provided and used services.To study the implementation of the model and its effectiveness, including parental and preschool teacher training and multisectoral collaborations.

We hypothesize that a coordinated working model with multiprofessional and intersectoral collaborations will promote early detection and support of preschool children with neurodevelopmental problems. We expect that this will also positively impact mental health and well-being in the long run. In addition, we hope that this working model enhances user satisfaction and the effectiveness of processes to provide services.

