### Study Design and Populations

Inclusion criteria include the following: a child referred to a child health care psychologist, aged 1.5-5 years, with ESSENCE (Early Symptomatic Syndromes Eliciting Neurodevelopmental Clinical Examinations) problems such as developmental delay, interaction, contact difficulties, language and communication difficulties, difficulties in everyday function, concentration/hyperactivity, self-regulation, acting/boundaries, and anxiety [1]. Exclusion criteria include the following: the family only needs parental support and/or there is a risk that participation in PLUSS would delay assessments or referrals to specialized services.

Detailed information about the study is given below. Research within PLUSS focuses on children, parents, and preschool teachers, and professionals working with the PLUSS are included in some substudies. Both cross-sectional and longitudinal quasi-experimental study designs are used. One substudy uses focus group interviews.

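### The Discussion promises prevalence of neurodevelopmental problems in preschoolers, but a sample of already referred children can give only the mix of problem types among those referred

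*Protocol article*

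**What the plan says.** The Discussion opens with the outputs the authors expect: "Expected results from this study include estimates of the prevalence of neurodevelopmental problems in preschoolers". The Background gives the context in which a reader will take that sentence. It cites a general figure, "Neurodevelopmental problems among preschool children are common, with an estimated 7%-10% prevalence", and then names a Swedish gap: "data on the current prevalence of significant neurodevelopmental problems among Swedish children aged 0-5 years are missing".

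The sampling frame is stated in three places:

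- **Abstract, Methods:** the population of interest is children aged 1.5-5 years "whom the child health care nurse refers for further assessment due to suspected neurodevelopmental problems".
- **Setting and Data Collection:** parents hear about the study once the child has been referred, and sign consent before the psychologist consultation.
- **Study Design and Populations:** inclusion requires "a child referred to a child health care psychologist, aged 1.5-5 years, with ESSENCE" problems. Families who need only parental support are excluded, as are children for whom taking part might hold up assessment or specialist referral.

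On detection, the hypothesis that follows the aims is that the coordinated model "will promote early detection and support of preschool children with neurodevelopmental problems". The process measures listed under Instruments are investigations, waiting time for assessment, visits and satisfaction. Table 1 gives assessments, visits and interventions as examples.

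**The concern.** A prevalence needs a numerator and a denominator drawn from the same defined population. Here the children were selected because they were thought to have the condition, so the sample is a filtered part of a numerator with nothing to divide by. Set beside the Background's remark about missing Swedish data, the Discussion sentence invites the reader to expect that gap to be filled.

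The article says results will reach policy makers. A percentage from referred children carrying the label of prevalence could mislead service planning. The limitations it names are the single county and loss to follow-up. Selection on referral is not among them.

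The early-detection wording raises a related but smaller question: whether anything the study records could show that children were found earlier, or that more of them were found.

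**Working it through.** **Is there a prevalence figure to reproduce?** No. The article gives no target estimate, precision or denominator for prevalence. The 7%-10% is a cited background value. The check is therefore on the sampling frame.

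**Step 1. What the sample returns.** Let D be having a neurodevelopmental problem and E being enrolled. Enrolment requires referral, ESSENCE problems, consent and no exclusion. Since E requires D, P(D | E) is about 1, whether P(D) is 0.07, 0.10 or anything else. The Abstract says problems are suspected, so a few enrolled children may not be confirmed, but the inclusion criterion asks for the problems themselves and the argument is unchanged.

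**Step 2. Does another substudy supply unselected children?** Table 1 lists a parent focus-group study, a pilot, the full-scale study and the parental training study. Each concerns children with neurodevelopmental problems or their parents. The comparison group (n=160) comes from parts of the county not yet in PLUSS and receives treatment as usual. It is not described as a population sample.

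**Step 3. Can the county figure rescue it?** Sample Size mentions approximately 860 children per year for the county without saying clearly what is counted. Suppose they were all the cases. The result is then 860 / D, with D, the number of preschool children, an assumption because the article does not give it:

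| Assumed D | 860 / D |
|---|---|
| 8,600 | 10.0% |
| 10,000 | 8.6% |
| 12,286 | 7.0% |
| 15,000 | 5.7% |
| 20,000 | 4.3% |

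The answer is set by a figure that the document does not contain.

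**Step 4. Is it a matter of sample size?** No. For an unselected sample, n = 1.96² × p(1 − p) / h². With h = 0.02:

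- p = 0.07: 3.8415 × 0.0651 / 0.0004 = 625.2, so 626 children.
- p = 0.10: 3.8415 × 0.09 / 0.0004 = 864.3, so 865 children.

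That is the same order as the target of 700. The obstacle is who is sampled, not how many.

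**Step 5. Detection.** The fraction of all children who are referred is prevalence times the probability of being detected. Taking 7%-10% from the article and assuming detection of 30% or 90%:

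- 0.07 × 0.30 = 2.1%; 0.07 × 0.90 = 6.3%
- 0.10 × 0.30 = 3.0%; 0.10 × 0.90 = 9.0%

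In all four cases the enrolled sample consists only of referred children with problems. The share with problems among them carries no information on how many were missed. Against this, the listed process measures (investigations, waiting time, visits, interventions, satisfaction) arise at or after referral. None is a detection rate, a count of missed cases or an age at detection.

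**The case against.** The best defence is that prevalence is not an objective. The three aims cover longitudinal problems and functioning, parental well-being and satisfaction, and implementation and effectiveness. Table 1 has no prevalence outcome and the sample size is not built on one. The claim is part of one Discussion sentence, and correcting it changes no recruitment, instrument or comparison. All of this stands, and it limits the reach of the point. It does not make the sentence right.

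A second defence is that frequencies of specific problem types (language, motor, self-regulation and so on) can be estimated. That also stands, provided they are labelled as frequencies among referred children. The 100% figure applies only to having any problem.

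On detection, a reader might infer that the study promises a test of early detection and that a main hypothesis is wholly untestable. The article does not support that reading. Detection is half of a compound hypothesis and is not in the aims, and the support half has listed process outcomes. Referral is for suspected problems, so identification continues afterwards: JA-OBS screens for the autism spectrum, and possible diagnosis and waiting time for assessment are recorded. Nor does the article say that controls enter only after detection. It gives where they come from and what care they receive, not their route of entry. Age at referral could serve as a weak proxy, although no such comparison is described.

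Finally, an article condenses a fuller protocol. That would excuse missing detail. Here the stated result conflicts with the stated frame.

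**Conclusion.** The point holds for prevalence. As described, the study cannot estimate the prevalence of neurodevelopmental problems in preschoolers, because the proportion with any problem is about 100% by inclusion against a cited population value of 7%-10%. It can estimate the distribution of problem types among referred, consenting children who are not excluded. This rests on the inclusion criteria and Table 1 being complete as to who is sampled. It does not depend on the power calculation or on how the 860 per year is read.

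The detection point is secondary and narrower: the listed outcomes do not include a detection rate or age at detection, so the early-detection half of the hypothesis has no matching measure. It would go too far to say that nothing about timeliness can be learned, since waiting time for assessment is collected.

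The consequence is for what the study may conclude. Its aims, comparisons and recruitment are untouched.

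**What to change.** 1. In Principal Findings, replace the prevalence claim with the distribution of problem types among referred children, and state that no proportion from this sample will be reported as population prevalence. Add selection on referral and consent to the limitations. This is a wording change and costs nothing.
2. Limit the hypothesis to support and to timeliness of assessment after referral, both of which have listed measures. This is also wording only.
3. As an optional alternative to item 2, keep early detection and give it outcomes: age at first referral, and aggregate referral counts per resident child aged 1.5-5 years, compared between PLUSS and not-yet-PLUSS areas. The Background reports that "Swedish child health care has a well-established screening program that reaches 95% of all preschool children", so the child health care service is the natural place to ask. The cost is a request for aggregate counts and a short description of the comparison. It would be an area-level addition to the plan.

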### Conclusions

PLUSS is an integrative working model with multiprofessional competence and intersectoral collaboration capacity to help preschool children with neurodevelopmental problems and their parents. The study has a quasi-experimental cross-sectional and longitudinal design. Data are collected from parents, health care providers, and preschool teachers and analyzed using quantitative and qualitative methods. The study is run in one Swedish county, and generalizability needs to be studied separately.

## Abbreviations

CEQ: Children’s Engagement Questionnaire
ESSENCE: Early Symptomatic Syndromes Eliciting Neurodevelopmental Clinical Examinations
JA-OBS: Joint Attention Observation tool
LAPS: *lapsen psykososiaalisen terveyden arviointimenetelmä* (child mental health assessment form)
PLUSS: *Psykisk hälsa Lärande Utveckling Samverkan kring Små barn* (mental health, learning, development, collaboration around preschool children)
SDQ: Strengths and Difficulties Questionnaire
